### Randomization and allocation concealment

After the screening visit, qualified subjects will be randomly assigned to either the AHP group, the APP group, or the waiting-list group in a ratio of 1: 1: 1. Random numbers will be generated by a third person ([name]) who is not practicing throughout the study, using the random number generator in the SPSS statistical software package (Version 22.0, SAS Institute Inc.). As the letters are drawn (A or B or C), they will be placed into opaque envelopes labeled with sequential numbers. The envelopes will be sealed and remain in numerical order in a safe place until the completion of surgery. The same researcher ([name]) (not involved in the study) will prepare the envelopes. However, it was not possible to conceal the allocation among the waiting-list group.

### Blinding

The herbal paste will be packed and labeled by the 3rd Affiliated Hospital of Chengdu University of TCM to ensure that the practitioner and the patients involved in the study will remain fully blinded as to the identity of the treatment administered. Therefore, the participants, clinical practitioners, the outcome evaluators, the data manager and statistician will not know the treatment allocations, which will not be revealed until the end of study. In addition, the practitioner will be instructed not to communicate with participants about the possibility of their allocation. However, blinding of the waiting-list group is not possible for this trial.

### Interventions

Acupoint plaster treatment will be performed by certified acupuncturists with at least 5 years’ clinical experience (Fig. 3a and b). All treatment details will be standardized between practitioners by guiding videos and relevant training before the first treatment session. The acupoint selection regimen was based on academic literature data mining [42] and expert opinions. Five acupoints will be used: *Shenque* (CV8), *Guanyuan* (CV4), *Qihai* (CV5), *Ciliao* (BL32) and *Zigong* (EX-CA1).

**Fig. 3 Fig3:**
[figure not shown]
Illustration of the sticky plaster. **a** and **b** show the anterior and posterior appearance of the acupoint plaster, respectively. **c** and **d** show the paste inside the plaster. **c** demonstrates the herbal plaster. **d** demonstrates the bluckwheat plaster. These two kinds of paste are indentical in appearance. The Figs. are only for illustrative purposes

In this study, there are two types of paste to be applied on the sticky plasters: herbal paste (HP) for the AHP group, and buckwheat paste (BP) for the APP group (Fig. 3c and d). The HP remedy in this study comes from an ancient Chinese herbal formula named *Shaofu Zhuyu Tang* (SFZYT) which was recorded in a TCM medical classic, *Yi Lin Gai Cuo (Correction of Errors in Medical Classics)*, which was written or recorded by *Qingren Wang* in 1830. Clinical studies have shown the positive effect of SFZYT on PD [43, 44]. A systematic review recently found the therapeutic effects of SFZYT on PD to be superior to drugs [45]. In addition, previous clinical observations [46–48] have demonstrated that the SFZYT was safe for acupoint plaster. Therefore, we adapted this formula and standardized its performance.

In the AHP group, the standard operating procedures (SOP) are listed as follows:Prepare the herbal materials: SFZYT includes *Angelicae sinensis Radix* (*danggui*), Rhizoma (*chuanxiong*), *Paeoniae Radix rubra* (*chishao*), *Cinnamomi cortex* (*rougui*), *Foeniculi fructus* (*xiaohuixiang*), *Zingiberis rhizoma (ganjiang*), Myrrha (*moyao*), *Trogopterus dung* (*wulingzhi*), Typhae Pollen (*puhuang*) and *Corydalis rhizoma* (*yanhusuo*). The ingredients of this formula are mixed in a weight ratio of 3: 1: 2: 1: 0.5: 2: 1: 3: 1: 1 and then the raw materials ground into fine powder (under 75 μm diameter) using a special Chinese medicinal crop powder mixer (manufactured by Royalstar Co., Ltd., Hefei, China)Add the liquid base: place the mixed herbal powder into a container, add honey and stir well to make a thick herbal pasteAdd the sticky plaster: put 10 g of the herbal paste onto a medical sticky plaster. Then apply the plaster over the acupoints. The sticky plasters are sized 5 × 5 cm^2^ with a 0.8-cm radius in the middle of which is placed the host herbal paste. The rest of the sticky plaster carries no herbal paste, which makes it adhere to the skin over the acupointsTreatment procedures: locate the acupoints, disinfect the skin, and attach the plaster on the skin over the acupoints. The plasters will be left on the skin for 4–8 h depending on each patient’s individual response because it must be removed immediately should any allergic reaction occur, which may be described by patients as a burning sensation, severe itchiness, blisters, pruritus or rash on the local skin. A total of nine sessions will be performed during the three menstrual cycles, the treatment starts 1 week prior to the menstruation, with one 6–8-h treatment three times per week, according to the subject’s estimated dates

For the APP group, the placebo paste is made of buckwheat flour without any herbal medicines; however is still mixed with honey to maintain a similar appearance to the AHP (Fig. 2c and d) so that the plasters used in these two experimental groups are undistinguishable to patients and practitioners. Moreover, the only variable between the AHP group and the APP group is the ingredients of paste. In order to reduce the bias caused by performance, all the rest of the clinical procedures remain the same.

No intervention will be performed in the WL group. The participants are required to continue their current living habits, including exercise and diet, while filling out related questionnaires throughout the full observational period of six menstrual cycles. To meet the requirements of the Rule of Ethics, all participant in the WL group will be offered free AHP treatment of their choice at the completion of the study.

With regard to quality control of the herbal plaster, we will take the following measures: (1) first, the herbal plaster will be prepared beforehand by the central pharmacy of the 3rd Affiliated Hospital of Chengdu University of TCM that meets the requirements of the regulatory guidance issued by the China Food and Drug Administration, (2) in addition, pre-job SOP training and examination will be provided by the principal investigator ([name]) to the practitioner for ensuring the quality of treatment procedures (i.e., locate the acupoints, disinfect the skin, attach the plaster on the skin over acupoints), (3) furthermore, the data and results will be monitored by the Evidence-based Medicine Center of Chengdu University of Traditional Chinese Medicine.

### Outcome measurements

#### Primary outcome

The primary outcome will be pain intensity reduction measured by the Visual Analog Scale (VAS). The severity of menstrual pain will be estimated using the VAS graded from 0 mm to 100 mm, indicating an absence of pain to the most serious pain imaginable [49].

#### Secondary outcomes

The secondary outcomes include the Cox Menstrual Symptom Scale (CMSS) [50], the 12-Item Short Form Health Survey (SF-12) [51], the Participant Global Impression of Change (PGIC) [52] and the DD.

#### Time points of outcome measurements

The VAS, CMSS, SF-12 and DD will be recorded at baseline and at every menstrual cycle throughout the treatment and the follow-up periods. The PGIC will be measured at the first, second, third, fourth, fifth and sixth menstrual cycles after inclusion.

We will estimate the expectation of participants to determine whether their expectations affected the outcomes by using the Credibility Expectancy Questionnaire (CEQ) [53, 54] at the baseline and the first to the third menstrual cycle before receiving treatment. In the proposed study, the questionnaire will be used to control for placebo effects, which are expected to be relatively high for light-therapy studies [54]. Blinding will be assessed by asking participants what group they thought they were in (AHP group or APP group, or “don’t know”) at the end of trial, and why they believed that they were in that group.

### Safety evaluation

Clinical adverse events (AEs) will be recorded throughout the study and graded using the National Cancer Institute Common Terminology Criteria for Adverse Events (CTCAE) version 4 [55]. According to previous randomized controlled trials (RCTs) [56, 57], the AHP may cause potential adverse events of itchiness, allergic responses of the skin or the whole body, local infections and other mild side effects. Any unexpected symptoms or signs during the treatment must be documented regardless of their relation to the study intervention. All details of related and unexpected AEs, such as time of occurrence, severity of AE, and suspected causes, will be recorded on Case Report Forms (CRFs). Participants with mild and moderate AEs will receive symptomatic treatment and will be closely followed up by the research team. Severe AEs will be reported to the Research Ethics Committee within 48 h.

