## Background

Primary dysmenorrhea (PD) is prevalent among adolescent girls and women of reproductive age [1]. The incidence of PD ranges from 45% to 72% of all menstruating women; moreover, among adolescent girls it can be as high as 93% [2, 3]. Its symptoms vary but typically include dull, throbbing and cramping pain in the lower abdomen during menstruation [4, 5]. Patients may also experience vomiting, nausea, diarrhea, fatigue, fever, headache, sleeplessness and backache [6, 7]. This widespread condition not only decreases social participation and the quality of life of women, but also causes significant financial losses due to inability to work and extra medical costs [8, 9].

Approximately 67% of patients with PD choose anodyne drugs to temporarily relieve pain [10]. Nonsteroidal anti-inflammatory drugs (NSAIDs) are well advocated as the first-line medication for PD [11]. However, the pharmacological treatment has been reported to be associated with adverse effects including indigestion, headache, drowsiness; and in 20%–25 of patients, failure to relieve the pain was reported [12]. Consequently, efforts have been made to identify effective, low-risk interventions [13, 14].

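### The only urgent safety report is triggered by severity, not seriousness, so an event that is serious by outcome but graded below severe has no stated urgent route

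*Protocol article*

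**What the plan says.** All the relevant rules stand in the Safety evaluation section of the protocol article.

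- Adverse events are recorded throughout the study and "graded using the National Cancer Institute Common Terminology Criteria for Adverse Events (CTCAE) version 4".
- Below the severe level: "Participants with mild and moderate AEs will receive symptomatic treatment and will be closely followed up by the research team".
- At the severe level: "Severe AEs will be reported to the Research Ethics Committee within 48 h".
- On what must be documented: "Any unexpected symptoms or signs during the treatment must be documented regardless of their relation to the study intervention".
- The details to be entered on the case report form are given by example: when the event occurred, how severe it was, and what is thought to have caused it. Seriousness is not among the examples.
- On foreseen reactions, citing previous randomized trials: "the AHP may cause potential adverse events of itchiness, allergic responses of the skin or the whole body, local infections and other mild side effects".

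The Background section describes the disease's own symptoms: "Patients may also experience vomiting, nausea, diarrhea, fatigue, fever, headache, sleeplessness and backache". The Abbreviations list has an entry for adverse events and none for serious adverse events.

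**The concern.** Severity and seriousness are different attributes of an adverse event. Severity is how intense it is. Seriousness is what it leads to, such as hospital admission or a threat to life. Expedited reporting exists so that a body able to act hears quickly about events with grave consequences, and the usual trigger for it is therefore seriousness.

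Here the trigger is severity. If the rule is applied as written, the investigator has a stated duty to report a severe event within 48 hours. For an event graded lower there is no such stated duty, whatever its outcome. At stake is whether the ethics committee hears in time of a reaction it would want to know about. The article reports recruitment as ongoing, so the wording bears on current participants.

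**Working it through.** No arithmetic applies: the article gives no figure on this point, and the question is what the reporting rule covers.

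**Step 1. What *severe* means here.** Three features of the Safety evaluation section point to intensity:
- events are graded on a named grading scale;
- the rule for severe events follows directly on the rule for mild and moderate ones, which gives the ordered series mild, moderate, severe;
- severity is named among the attributes to be recorded, and seriousness is not.

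**Step 2. Whether another urgent route is stated.**
- Safety evaluation: one recipient (the ethics committee), one deadline (48 h), one trigger (severe).
- Interventions: says what happens to the plaster when the skin reacts, which is not a notification rule. It also gives an evidence-based medicine centre the monitoring of data and results, with no urgent reporting role described.
- Data integrity: covers form checks, queries and data entry only.
- Abbreviations: no entry for serious adverse events.

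No second route and no definition of seriousness appears.

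**Step 3. Cross-classify events by the two attributes.**

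| | Graded severe | Graded mild or moderate |
|---|---|---|
| Serious by outcome | 48 h report | No urgent report stated |
| Not serious by outcome | 48 h report | No urgent report stated |

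The two rows are identical, so under the stated rule seriousness plays no part in what is reported. The gap is the upper right cell.

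**Step 4. Whether the upper right cell can be sized.** It cannot. Its size depends on how the grading scale treats events with grave outcomes, and on how often such events occur. The scale is cited but its definitions are not reproduced, and no event rates are given. The article does foresee whole-body allergic responses and local infections, so reactions whose outcome could matter are within its own expectations. It does not show what grade they would receive.

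**Step 5. Usual menstrual symptoms.** The Background lists vomiting, headache and fever, among others, as features of the disease. The Safety evaluation section asks for unexpected symptoms to be documented, which suggests that usual ones are outside it. The Cox Menstrual Symptom Scale and the Dysmenorrhea Diary record symptoms at every cycle as secondary outcomes. Yet adverse events are to be recorded throughout, with no express exclusion of disease symptoms. Whether a severe but usual symptom falls under the 48-hour rule is left open.

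**The case against.** **The article is a condensation.** Definitions of serious events and further reporting routes are commonly left to the full protocol, and their absence here is not in itself a fault. That stands. It is also why one cannot say that a serious event of lower grade would go unreported: a reader might infer this, but the article is silent on such events and does not exclude reporting them. What remains is that the article does state a trigger, a recipient and a deadline, and the trigger is severity.

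***Severe* may be loose wording for *serious*.** The Primary outcome section uses *serious* for pain intensity, so the two words may have been interchanged. This is possible, but the direct sequence after mild and moderate makes it the less natural reading. If it is the right one, the sentence still needs correcting.

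**The gap may be small.** The grading scale may place most events with grave outcomes at severe or above. This cannot be settled from the article, and it limits what can be claimed about size. In addition, adverse events are recorded and graded whether or not they are reported urgently, so the 48-hour rule does not decide what reaches the safety data.

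**Stronger readings that the text does not support.**
- A reader might infer that severe disease symptoms will be reported every cycle, including in untreated women. The reference to unexpected symptoms, and the separate capture of menstrual symptoms as outcomes, speak against this. It is an open question, and no number of surplus reports can be derived because no rate is given.
- A reader might take "allergic responses of the skin or the whole body, local infections and other mild side effects" as labelling whole-body allergy and infection as mild. The sentence summarises what previous trials suggest may occur. It is not a grading instruction.
- A reader might note that close follow-up is stated only for mild and moderate events. For severe events this is silence, which an article may leave to the full protocol.

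**Conclusion.** The point holds in limited form. The article's only expedited report is keyed to intensity and not to outcome, and it states no urgent route for an event that is serious but graded below severe. This rests on reading *severe* as a grade, which the surrounding sentences support, and on the article as shown; the full protocol may differ.

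The frequency of affected events is unknown and cannot be estimated from the document. No sample size, estimate or test depends on the rule. It is worth correcting because it concerns participant protection and costs almost nothing. The status of usual menstrual symptoms is a related ambiguity for the authors to clarify, not a demonstrated error.

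**What to change.** 1. In Safety evaluation, make the trigger for the 48-hour report serious adverse events of any grade, citing the standard seriousness definition. Severe events may stay in the rule as well if the sponsor wishes.
2. Add a serious yes/no field to the adverse event form.
3. If the full protocol already uses *serious*, correct the article to match it.
4. State whether usual menstrual symptoms that are already captured by the Cox Menstrual Symptom Scale and the diary count as adverse events for this report.

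The cost is one or two sentences and one form field. No visit, outcome or analysis changes.

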### Sample size calculation

A few scientific trials have investigated the biomechanical effects of acupoint plaster on PD; however, the research methodologies are not appropriate to reference the determination of sample size to this study. The article being used for our study, was from an acupuncture clinical report with the use of VAS scores [16]. Liu’s study reported that patients who received classical acupoint achieved a mean reduction of 36.1 in VAS after acupuncture; while patients who received non-acupoint treatment showed a worse score of 29.9. Therefore, the decrease in VAS score of the three groups was predicted to be 38, 29 and 26, respectively. Using a bilateral test with an alpha value of 5% and a power of 80%, standard deviation for each group was 20 mm. According to the calculation with PASS software (Version 11.0, NCSS, LLC. Kaysville, UT, USA) in a 1:1:1 ratio, the effect size is 0.2550 of 51 participants in each group. The sample size is also calculated using the following formula [58]:$$ n\kern0.5em =\kern0.5em 2{\left(\sigma \frac{z_{1-\alpha /\left(2\tau \right)}+{z}_{1-\beta }}{\mu_A-{\mu}_B}\right)}^2. $$

Allowing for a 15% dropout, the sample size was increased to 60 per group, making a total of 180.

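### The planned AHP-APP difference of 9 mm is presented as following from a source that shows 6.2 mm; the step is unexplained, and the stated power does not hold at the source values

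*Protocol article*

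**What the plan says.** In the protocol article, *Sample size calculation* sets aside earlier plaster trials as unsuitable and names one other basis: "The article being used for our study, was from an acupuncture clinical report with the use of VAS scores". Patients treated at classical acupoints "achieved a mean reduction of 36.1 in VAS after acupuncture", "while patients who received non-acupoint treatment showed a worse score of 29.9". The next sentence draws the planning values from this: "Therefore, the decrease in VAS score of the three groups was predicted to be 38, 29 and 26, respectively". In the order in which the article lists the arms, these are AHP, APP and waiting list (WL).

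The other inputs are "Using a bilateral test with an alpha value of 5% and a power of 80" per cent, and "standard deviation for each group was 20 mm". The result is given as "the effect size is 0.2550 of 51 participants in each group", raised to 60 per group (180 in total) for 15% dropout.

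*Methods of statistical analyses* plans tests of AHP against APP and of APP against WL. The *Discussion* calls the first of these the specific effect of the plaster.

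**The concern.** The source figures and the planning figures stand in adjacent sentences, joined by the word *Therefore*, but the second set does not follow from the first. The active value rises by 1.9 and the control value falls by 0.9. Rounding explains neither: 36.1 does not round to 38, nor 29.9 to 29. Both shifts widen the gap and so reduce the sample needed. The section gives no minimum important difference, pilot result or other reason.

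What is at stake is how the trial is read. A reader of this section will believe that the trial was sized for the effect seen in its source. If AHP versus APP then turns out non-significant, that reader may take it as evidence against an effect of that size, when the trial had limited power to detect one.

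**Working it through.** **Inputs.** All come from *Sample size calculation*: planned decreases 38, 29, 26; source values 36.1 and 29.9; SD 20 mm; two-sided alpha 0.05; 51 per group before dropout and 60 after. The source's 29.9 is loosely described. I read it as a reduction on the same 0-100 mm scale, the only reading that fits the planned 29. The source SD is not quoted, so SD 20 is kept throughout.

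**1. The plan's own figure.** For one-way ANOVA, f = sqrt(mean of squared deviations of the group means) / SD.
- Grand mean = (38 + 29 + 26)/3 = 31; deviations 7, -2, -5; squares 49 + 4 + 25 = 78; 78/3 = 26.
- f = sqrt(26)/20 = 0.25495, the stated 0.2550.
- Noncentral F power is 79.6% at 50 per group and 80.5% at 51, so 51 is the smallest adequate n. 51/0.85 = 60; 3 × 60 = 180.

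Everything reproduces. The 80% is therefore the power of the three-group test. The printed pairwise formula at 9 mm gives 78, 94 or 104 per group for tau = 1, 2 or 3, never 51.

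**2. Source against plan.**
- Source: 36.1 - 29.9 = 6.2 mm. Plan: 38 - 29 = 9 mm. Ratio 9/6.2 = 1.45.

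**3. AHP versus APP power** (noncentral t, no multiplicity adjustment). Noncentrality = difference / (20 × sqrt(2/n)).

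| Difference | n per arm | Noncentrality | Power |
|---|---|---|---|
| 9 mm | 51 | 9/3.96 = 2.27 | 61% |
| 9 mm | 60 | 9/3.65 = 2.46 | 69% |
| 6.2 mm | 51 | 6.2/3.96 = 1.57 | 34% |
| 6.2 mm | 60 | 6.2/3.65 = 1.70 | 39% |

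**4. Three-group power with 36.1 and 29.9.** The quoted source figures include no untreated arm, so the WL mean must be assumed. I take three values: 26.9 keeps the planned 3 mm gap below APP, 26 keeps the planned value itself, and 23.9 doubles the gap to 6 mm.

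| Assumed WL mean | f | Planned f / this f | Power at 51 | Power at 60 |
|---|---|---|---|---|
| 26.9 | 0.192 | 1.33 | 55% | 62% |
| 26 | 0.208 | 1.23 | 62% | 70% |
| 23.9 | 0.249 | 1.02 | 78.5% | 85% |

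**5. Precision of a pairwise difference.** Half-width of the 95% CI = 1.96 × 20 × sqrt(2/n): 7.8 mm at 51 per arm and 7.2 mm at 60. Both exceed 6.2 mm.

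**The case against.** A planning effect need not equal that of a proxy source. The article calls its values predicted and says why it had to go outside the plaster literature. The contrasts also differ: the source compares point locations, while here, according to *Interventions*, only the paste differs between AHP and APP. The source therefore does not settle whether the true gap should be larger or smaller than 6.2 mm. This stands, and 9 mm could be a legitimate choice. But the article does not argue for it; it presents it as a consequence of figures that do not yield it.

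Four stronger readings are tempting, and the documents do not support them.

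- *The sample size arithmetic is wrong.* It is not; step 1 reproduces every figure.
- *The 80% rests on an effect 45% too large.* The 45% applies to the AHP-APP difference. The 80% belongs to the three-group test, where the excess in f is 33%, 23% or 2% depending on the WL mean. For the same reason 62% should not be quoted alone as the corrected three-group power.
- *The mismatch takes AHP versus APP power from 80% to 34%.* The 80% never applied to this contrast. The mismatch accounts for the fall from 61% to 34% at 51 per arm; the rest comes from sizing on the three-group test.
- *The trial cannot exclude a 6.2 mm effect.* Exclusion depends on the estimate. At 51 per arm an estimate below 6.2 - 7.8 = -1.6 mm would exclude it; at 60 per arm, one below 6.2 - 7.2 = -1.0 mm.

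The plan also promises 95% confidence intervals, which lessens the risk of misreading but does not correct the stated basis for the sample size.

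**Conclusion.** The point holds as an unexplained planning assumption presented as a derivation. The planned AHP-APP difference is 2.8 mm (45%) larger than that of the only source named for it. At the source difference, AHP versus APP power is 34% at 51 per arm and 39% at 60, so even with all 60 per arm analysed a true effect of that size would be missed about three times in five. Three-group power at 51 per arm would be about 55% to 78.5% over the WL means considered; at the top of that range the shortfall from 80% nearly disappears.

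These figures assume SD 20 in each arm and a single comparison of the VAS decrease, as the plan's own calculation does. A repeated-measures model could have different precision, but the article gives no inputs for one. The pairwise figures do not depend on the WL mean.

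**What to change.** In *Sample size calculation*, with no change of N:

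- Remove *Therefore*, and state that 9 mm is a planning assumption larger than the 6.2 mm in the source. If there is a reason for it, such as a minimum important difference, give it.
- Label the 80% as the power of the three-group test. Beside it, report AHP versus APP power at 6.2 mm (34% at 51 per arm, 39% at 60) with the 9 mm comparators (61% and 69%), and the range of three-group power over the assumed WL mean (about 55%, 62% and 78.5% at 51 per arm for 26.9, 26 and 23.9).
- State that the expected 95% CI half-width for a pairwise difference (about 7.8 mm at 51 per arm, 7.2 mm at 60) exceeds 6.2 mm. A non-significant AHP-APP result must therefore be read from its confidence interval and not taken by itself as evidence against a source-sized effect.

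The cost is a few sentences and a less favourable stated power.

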## Methods/design

### Study design

This proposed study is a single-centered, randomized, placebo-controlled trial which was devised following the Consolidated Standards of Reporting Trials (CONSORT) Statement recommendations [40] and the Standardized Protocol Items: Recommendations for Interventional Trials (SPIRIT) guidelines Additional file 1 [41]. Ethical approval has been obtained from the Institutional Review Board (IRB) of the Teaching Hospital of Chengdu University of Traditional Chinese Medicine (Approval No. 2016KL–003). We registered the study on the Chinese Clinical Trial Registry (Registration No. ChiCTR-IOR-16008701) in 2016.

The study will take place in the 3rd Affiliated Hospital of Chengdu University of TCM. During a run-in period of three menstrual cycles prior to randomization, the patients will be required to complete a Dysmenorrhea Diary (DD) and record related symptom scores every month to establish an individualized baseline score. A total of 180 subjects meeting the including criteria will be allocated randomly to three research groups that include one experimental group of the AHP and two control groups of the acupoint placebo plaster (APP) group and the waiting-list WL group. After randomization, subjects in the AHP and APP groups will receive treatments for another three menstrual cycles. Follow-up assessments through telephone calls or social media smartphone application will be processed for the last period of three menstrual cycles until the completion of study. Altogether it takes 9 months of three stages with three period cycles in each session. (See Fig. 1 for the study flowchart, and Fig. 2 for the assessment schedule).

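### The stated 80% power holds only for a three-group F test that uses an unsourced waiting-list fall of 26 mm; the planned APP vs WL contrast is 3 mm and has about 12–13% power

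*Protocol article*

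**What the plan says.** In the protocol article, under Sample size calculation, the planning values come from one acupuncture report. Two figures are quoted from it. The first is for the active arm: "patients who received classical acupoint achieved a mean reduction of 36.1 in VAS after acupuncture". The second, 29.9, is for the comparison arm, which was treated at non-acupoints. The next sentence reads: "Therefore, the decrease in VAS score of the three groups was predicted to be 38, 29 and 26, respectively". That sentence does not name the arms in order; the article's usual order is AHP, APP, WL.

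The same paragraph gives a two-sided alpha of 5%, power of 80% and a common spread ("standard deviation for each group was 20 mm"). It reports an effect size of 0.2550 with 51 per group from PASS, prints a pairwise formula, and raises the number to 60 per group for 15% dropout. The 80% is not tied to a named comparison.

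The Interventions section confirms what the third arm receives: "No intervention will be performed in the WL group". The Discussion, in the abstract and in the main text, makes AHP vs APP (specific effect) and APP vs WL (non-specific effect) the two contrasts that the trial sets out to investigate. Methods of statistical analyses plans a test of each through time-by-intervention interactions in mixed-effect models, alongside a three-group repeated measures ANOVA.

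**The concern.** Three planned falls are presented as following from two quoted figures. Both quoted figures belong to treated patients, so neither yields a value for women who receive nothing. The 26 mm therefore enters the calculation without a stated basis.

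Two consequences follow. First, the effect size and the number per group depend on 26, so the headline power is only as secure as that figure. Second, 26 set beside 29 fixes the planned non-specific effect at 3 mm. If the trial cannot detect an effect of that size, a reader who sees 80% power will misread a null APP vs WL result as showing no placebo effect. Likewise, a reader who takes the three-group test as the powered test may credit a significant result to the herbs when the waiting list alone produced it.

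**Working it through.** **Inputs.** From Sample size calculation: falls of 38 (AHP), 29 (APP) and 26 (WL) mm, SD 20 mm, two-sided alpha 0.05, power 80%, 51 per group, 15% dropout.

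**Step 1: reproduce the plan's figures.** For a one-way F test with k = 3 groups, the effect size is f = √(mean squared deviation of the group means) / SD.
- Mean of 38, 29, 26 = 31. Deviations: 7, −2, −5. Mean square = (49 + 4 + 25)/3 = 26.
- f = √26 / 20 = 0.2550, as stated.
- Noncentrality λ = 3·n·f². At n = 51, λ = 3 × 51 × 0.065 = 9.945, and noncentral F with 2 and 150 df gives power 80.5%. At n = 50 power is 79.6%, so 51 is the smallest n.
- 51 / 0.85 = 60, as stated.

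The arithmetic is right for this test. The printed pairwise formula, n = 2[σ(z₁₋α/(2τ) + z₁₋β)/(μA − μB)]², does not give 51 for any pair of the planned means. With τ = 1, 2 and 3 it gives 78, 94 and 104 per group for AHP vs APP (9 mm), and 44, 53 and 59 for AHP vs WL (12 mm). APP vs WL is in step 3.

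**Step 2: vary only the WL fall** (38, 29 and SD 20 held; the alternative WL values are assumptions, because the document gives none).

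| WL fall (mm) | f | Power at 51 per group | n per group for 80% |
|---|---|---|---|
| 29 | 0.2121 | 64% | 73 |
| 27 | 0.2392 | 75% | 58 |
| 26 (plan) | 0.2550 | 80.5% | 51 |
| 25 | 0.2718 | 86% | 45 |
| 20 | 0.3674 | 99% | 25 |

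One millimetre either side of 26 moves the required number by 6 to 7 per group.

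**Step 3: APP vs WL on the plan's own values.** Difference = 29 − 26 = 3 mm, SD 20.
- Required n at unadjusted alpha 0.05: 2 × [20 × (1.960 + 0.842)/3]² ≈ 698 per group. The printed formula with τ = 2 or 3 gives 845 or 931.
- Power of a two-sample t test: about 12% with 51 per group and 13% with 60.
- Smallest difference detectable with 80% power (noncentral t): 11.2 mm with 51 per group, 10.3 mm with 60.

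**Step 4: what a significant three-group test shows.** Suppose the herbs add nothing, so that AHP and APP both fall 29 mm (51 per group, SD 20).
- WL 26: means 29, 29, 26; f = √2 / 20 = 0.0707; probability of significance 11%.
- WL 20: means 29, 29, 20; f = √18 / 20 = 0.2121; probability 64%.

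How often this test succeeds without any herbal effect is thus decided by the WL fall.

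**The case against.** The best defence is that nothing is miscalculated and the direction of error is mostly harmless. 0.2550, 51 and 60 all reproduce. If untreated women improve by less than 26 mm, the three-group test gains power, so 26 would be a cautious choice for that test; only a WL fall above 26 lowers its power. Both points stand. This is an unsupported assumption and a power figure with too wide an apparent reach, not an arithmetic error, and it does not show that 51 is too small for the three-group test.

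It is also fair that a condensed article may omit a source, and that the cited report is not at hand. The claim is therefore only that no basis for 26 is stated here, not that the report contains none. Separate pairwise tests are planned, and nothing in the article says that a significant three-group result will be read as AHP beating APP. The closing statement in the fix is a safeguard.

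A mixed-effect model over several cycles may be more precise than a single comparison at SD 20. For 3 mm to reach 80% power with 51 per group, however, the effective SD would have to be about 20 × 3/11.2 = 5.4 mm. The article gives nothing that supports such a reduction.

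Some stronger readings are tempting but not supported:
- A reader might infer that 3 mm contradicts the plan's own expectation, since the time-points section speaks of using the questionnaire to "control for placebo effects, which are expected to be relatively high for light-therapy studies". That expectation is tied to light-therapy studies, which this trial is not, and the main Discussion gives no size for placebo effects.
- A reader might apply 26 mm to a woman at the 40 mm entry limit and call the resulting 14 mm absurd. The 40 mm is a floor for entry, while 26 mm is a group mean.
- A reader might want the run-in, where women "record related symptom scores every month to establish an individualized baseline score", to supply the WL value. Those cycles precede randomisation and overlap the baseline used for selection, so change within them is not the baseline-to-treatment-period change that the WL figure represents.

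**Conclusion.** The concern holds in a limited form. No basis is stated for the 26 mm, and the effect size, the 51 per group and the 80% power apply only to a three-group F test that uses it. On the plan's own values the APP vs WL contrast is 3 mm, with 12–13% power at 51 to 60 per group against roughly 698 needed. The 80% therefore does not carry over to one of the two contrasts that the trial declares as its aim.

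This rests on SD 20 mm in every arm, the arm order AHP, APP, WL, a two-sample comparison at unadjusted alpha 0.05, and assumed alternatives for the WL fall. It does not show that 26 is wrong or that more patients are required for the three-group test.

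**What to change.** Keep 60 per group and rewrite the sample size paragraph to:

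1. State that 80% power applies only to the three-group test, under an assumed WL fall of 26 mm.
2. Give the basis for 26 mm, or label it an assumption, and show power over a range of WL falls, as in the table above.
3. State that APP vs WL can detect about 11 mm with 51 per group or 10 mm with 60, at 80% power and SD 20 mm, so that a non-significant result there is not evidence of no placebo effect.
4. State that a significant three-group test is not evidence for AHP over APP; that question rests on the planned AHP vs APP test.

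This costs a reworded paragraph and a short sensitivity table, with no extra patients and no unblinding. The drawback is that the stated power becomes less favourable.
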